### Patient and public involvement

The research question originates from the practical problems arising from the publications in recent years. No patient was involved in the development of the research question, outcome measures, or study design. Complex bAVMs could hardly receive a satisfying clinical prognosis with any single method. Although some of the patients are suffering from intractable epilepsy or microhemorrhage, which are considered to be operative indications, the expectant therapy is the most common method. Referring to the present study on one-staged hybrid operation, the advantages of microsurgical and endovascular embolization were significantly integrated as mentioned above. A new therapeutic concept was proposed by this novel technique. Most importantly, patients with complex bAVMs have a chance to be cured. The study is designed to validate the efficiency and safety of the one-staged hybrid operation. With the development of microsurgical skills and life-sustaining technology, neural function deterioration caused the most concern among outcomes. It is the main reason deterring the patients from operation, as well [6, 7, 9, 10]. For this reason, the neural function deterioration is chosen to be the primary outcome in this study. Traditional outcomes, such as postoperative mortality, operation-related complications, and bAVMs residue, are extracted to secondary outcomes as evaluating indexes.

The final results of the study will not be disseminated to the study participants but will be published in research articles. In the beginning of the study, as there was no reference result, the benefits, risks, and possible prognosis were acknowledged in preoperative discussions among neurosurgeons, interventional radiologists, and anesthesiologists before the study participants were informed. After a certain amount of cases are accumulated, the participants will be informed of the latest results as the risk reference.

All patients involved are introduced to the operative process, advantages and shortcomings of one-staged operation and traditional operation. Individualized risks of the two methods are evaluated in the preoperative discussion and announced to the patients. Participants make the selection after weighing the benefits, risks and financial burden of different operative methods. As the majority of medical expenses are covered by the Urban Residents’ Basic Medical Insurance and Rural Cooperative Medical Service for Chinese citizens, there is no extra financial compensation in this study.

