### Study design

The study consists of 2 parts: the registry set and the trial set. The two sets of this study share a common data pool, which contains all the enrolled patients. The registry set is designed as a multicentric, prospective, real-world registry (Research on Hybrid Operation Technique in the Treatment of Complex Brain Arteriovenous Malformations; ClinicalTrials.gov ID: NCT 03774017), and it occupies the whole data pool. The patients involved will receive traditional operation (TO) or one-staged hybrid operation (HO) and will be registered in the corresponding TO group or HO group. End points will be evaluated at scheduled time points. The safety and efficiency of the one-staged hybrid operation in treating complex bAVMs will be validated. The trial set is designed as a multicenter, prospective, pragmatic clinical trial (PCT). Patients in this set will be registered in the registry set in the meantime. PCT is a real-world modification of randomized clinical trial (RCT), consisting of an RCT part and a registry part. Patients have the right to choose the part in which they want to participate. The candidates in this set are patients harboring bAVMs with perforating arterial (PA) feeders. To them, an extra written informed consent is required. Patients who agree to take part in the RCT part will be randomly assigned to the HO or TO group and receive the corresponding treatment. Both of the sets share the same end points. The purpose of the trial set is to validate the benefits and risks of hybrid operation for lesions with perforating arterial feeders and the contribution of endovascular embolization. A strategy of multicenter stratified blocked randomization is used in the central randomization system (CRS), which is contained in Electrical Data Capture (EDC) system. When registering a participant in EDC system in the trial set, CRS generates an assignment result according to the demographic information. Each center is set as a stratifying level, which could reduce the differentiation of sample size between groups. The blind codes, generated by statistician, remain blind during randomizations to avoid potential selection bias. The design of this study is presented in Fig. 1. The grouping assignment is blinded to outcomes assessors. Both sets will be conducted between Jan 2016 and Dec 2020. The study is hosted by Beijing Tiantan Hospital, with the participation of 20 cooperation centers, including academic, military, and other public hospital (Table 1).

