### Group assignment and treatment

In the registry set, patients will be assigned to the TO group or the HO group on the basis of clinical conditions and personal wishes. Patients in the HO group will receive microsurgical operation under the assistance of endovascular embolization or balloon occlusion. Patients in the TO group will receive only traditional microsurgical operations, and a repeated DSA will be arranged 3 days after the operation.

In the trial set, patients who refuse the randomized group assignment will be enrolled in the registry set. Those who agree will be randomly (by central randomization system) assigned to the TO group or the HO group. The interventions of each group will be the same in the two sets.

The functional MRI-based neuro-navigation and intraoperative Doppler ultrasound will be used as essential assistance in all operations.

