### Outcome evaluation

The primary outcome is defined as neural function deterioration (an increased mRS and mRS > 2) in the 3 months after operation. The neural function will be evaluated 48 h and 7 days after operation while hospitalized and at 3 months, 6 months and 12 months after discharge. A deterioration will be considered temporary if it is sustained < 12 months, otherwise it will be considered permanent. The secondary outcomes will include the postoperative mortality, operation-related complications, and bAVMs residue. The postoperative mortality will include death that occurs within 7 days from the date of operation. Operation-related complications will include any complications that occur within 7 days from the date of operation, including intracranial hemorrhage or infarction, infection of the central nervous system, infection of the respiratory system, cranial nerve deficits, and other symptomatic complications. The bAVMs residue will be diagnosed on the basis of DSA or CTA after operation. The mRS fluctuation will also be recorded and defined as the consecutive changing value of mRS between different follow-up points. The evaluations and diagnoses will be conducted by the physicians who have not learnt about the patients and collected by CRCs.

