### Data management

All the data in this study will be sourced from experienced physicians and radiologists in 20 participating centers, and they will be prospectively collected by full-time clinical research coordinators (CRCs) using both paper documents and a web-based electronic data capture system (EDC system). SUN HEALTH (Beijing) Health Care Group, a third-party CRO, is contracted to render the services of quality control and data management. The study is supervised and administered by the Ministry of Science and Technology of China and the Beijing Municipal Science and Technology Commission, and it receives resource support from the China National Clinical Research Center for Neurological Diseases. Issues that occur in the cohort will be reported to oversight authorities and evaluated. All data are available only to participating centers while the study is being conducted and will become public once the study concludes. All of the processes of data collection, statistical analysis, study result interpretations and dissemination are under the direct supervision of the principal investigator. The final results will be disseminated via printed media in December 2020.

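### Telling new participants the latest study results during recruitment makes enrolment period a confounder in the registry comparison and can change who accepts randomisation

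*Protocol article*

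**What the plan says.** The Patient and public involvement section describes counselling that changes over the study. Early participants were counselled without study data ("In the beginning of the study, as there was no reference result"). Later, "After a certain amount of cases are accumulated, the participants will be informed of the latest results as the risk reference". Neither the number of cases that triggers this nor the content of the results is fixed. The same section says that the final results will not be sent to participants.

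The information given feeds two decisions:

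- **Choice of operation (registry set).** "Participants make the selection after weighing the benefits, risks and financial burden of different operative methods" (Patient and public involvement), and "patients will be assigned to the TO group or the HO group on the basis of clinical conditions and personal wishes" (Group assignment and treatment).
- **Consent to randomisation (trial set).** "Patients have the right to choose the part in which they want to participate" (Study design), and "patients who refuse the randomized group assignment will be enrolled in the registry set" (Group assignment and treatment).

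The primary outcome is "an increased mRS and mRS > 2) in the 3 months after operation" (Outcome evaluation), so results become available well inside a five-year recruitment. The Statistical analyses section plans comparisons between homogeneous cases and logistic regression on demographic, history, lesion, angioarchitecture and admission variables. Enrolment period is not in that list.

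**The concern.** In a registry where patients and clinicians choose the operation, group membership already depends on prognosis and preference. Releasing accumulating results adds a dependence on time: patients counselled before and after the release choose on different information. If the deterioration rate also changes over the years, for example as teams gain experience with a new operation, the group with more late patients takes the rate of the later period. The crude HO/TO difference then mixes a period effect with the treatment effect. Adjusting for patient and lesion characteristics need not remove it.

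In the trial set, a candidate who has been told early results may be less willing to be randomised. What is at stake there is the pace of recruitment and the type of patient who consents.

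**Working it through.** **Does the plan create the dependence?** Put the sections side by side. Information changes at an unspecified time during recruitment (Patient and public involvement). The registry operation is chosen partly on that information (same section; Group assignment and treatment). Consent to randomisation is optional (Study design; Group assignment and treatment). So allocation in the registry, and entry to the randomised part, can both depend on calendar time and on earlier outcomes.

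**How large could the registry effect be?** The article gives no figure for time trends or for changes in HO uptake, so the following values are assumptions.

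- Two equal-sized halves of recruitment, with results released at the midpoint.
- No treatment effect: deterioration is 40% in the first half and 30% in the second, in both groups.
- HO share is 50% in the first half and 80% in the second. The overall share is (0.50 + 0.80)/2 = 65%, close to the planned 800/1200 = 66.7% (Sample size, Registry set).

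Crude HO rate = (0.50 × 0.40 + 0.80 × 0.30)/(0.50 + 0.80) = 0.44/1.30 = 33.8%.

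Crude TO rate = (0.50 × 0.40 + 0.20 × 0.30)/(0.50 + 0.20) = 0.26/0.70 = 37.1%.

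Spurious difference = 37.1 − 33.8 = 3.3 points in favour of HO. Within each half the difference is zero, so in this illustration adjustment for period removes the whole bias.

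**Range.** With HO shares h1 and h2 in the two halves and a fall of d in both groups, the difference is d × [h2/(h1 + h2) − (1 − h2)/(2 − h1 − h2)].

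| Assumed fall | HO share, first to second half | Spurious difference |
|---|---|---|
| 10 points | 50% to 80% | 0.10 × (0.615 − 0.286) = 3.3 points |
| 5 points | 50% to 80% | 0.05 × (0.615 − 0.286) = 1.6 points |
| 10 points | 60% to 70% | 0.10 × (0.538 − 0.429) = 1.1 points |
| none | any | 0 |
| any | no change | 0 |

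If rates rise over time, or uptake of HO falls, the sign reverses.

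**Against the plan's own yardstick.** The registry aim is to cut a rate of 38.6% by 10% (Sample size, Registry set). Read as 10 percentage points, 3.3 points is a third of the aim.

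**Trial set.** Consent comes before central allocation, and blocks are stratified by centre (Study design). Both arms are therefore filled in parallel over calendar time within each centre, and a period trend affects them alike. No comparable bias arises.

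**The case against.** Several points on the other side have force.

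- **The registry is confounded by choice in any case.** True. Regression is planned, and operation dates are recorded (Study participants), so period could be added in the analysis plan. But the release of results is a deliberate change in how patients choose, and it is cheap to allow for it now.
- **The results shared may not be comparative.** The sentence does not say that they are given by arm; overall risk, or risk under HO alone, would fit the wording. This stands, and it limits the trial-set concern to the case where by-arm results are shared.
- **Patients deserve current risk information on a new operation.** This also stands. A fixed pre-study risk statement for everyone throughout recruitment would be a debatable trade, and it is not proposed here.

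A reader might also infer more than the article supports:

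- **That centres have open access to results by arm.** The Data management section says "All data are available only to participating centers while the study is being conducted" and then announces public release after the study ends. That restricts outsiders. It does not say that each centre sees other centres' outcomes or comparative summaries.
- **That the 0.05 test loses its level.** No stopping rule or change of sample size is tied to the shared results, and the trial-set size is fixed at 236. Looking without acting on the sample size does not inflate the error rate.
- **That power falls.** If only 70% of 236 were randomised (about 83 per arm), power at 38.6% versus 19% would be about 0.80. But the 70% has no source in the article, and the Strengths and limitations section insists that the trial set's lower limit on sample size be kept. Lower acceptance then means slower recruitment, not a smaller trial.
- **That the randomised comparison is biased.** Concealed central randomisation protects it, and outcome assessors are blinded. A changing mix of consenting patients bears on generalisability, not on the validity of the contrast.

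**Conclusion.** The concern holds for the registry set. Followed as written, the plan lets the HO/TO mix depend on calendar time and on early results, and the listed analysis variables do not cover period. The size is unknown. On the assumed values it is 1.1 to 3.3 points of spurious crude difference, and it needs both a time trend in deterioration and a shift in uptake. If either is absent, there is no bias from this source.

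For the trial set the conclusion is narrower: if by-arm results are shared, they can alter who accepts randomisation and slow recruitment. The randomised contrast stays valid, and no claim is made about its error rate, its power or centres' access to data. The absence from the article of a monitoring committee or formal interim rules is not relied on, since a fuller document may hold them.

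**What to change.** 1. Amend the sentence in Patient and public involvement so that by-arm outcomes of randomised patients are not released to participants or treating surgeons until trial-set recruitment and primary (3-month) follow-up are complete. Safety concerns go to the oversight authorities mentioned under Data management, who decide on disclosure.
2. Record the date on which any registry results are first used in counselling.
3. Add enrolment period to the registry logistic regression, either as before/after that date or as calendar year, taken from the operation dates already collected. This also works for patients already enrolled.

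Surgeons will still know how their own patients fared. By the article's capacity figures the host hospital performs about 220 of 240 cases a year (92%), so the restriction concerns tabulated comparative results and cannot remove all impressions. The cost is a wording change, one recorded date, one extra covariate, and somewhat less current counselling on the randomised comparison.

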### Study participants

Patients harboring bAVMs will be regarded as candidates for the duration of the study. Those candidates will be further screened with inclusion and exclusion criteria by attending physicians in all the participating centers. Patients will be involved after giving their written informed consent. Demographic information (age, gender, race, provenance, occupation) will be recorded as baseline features. Present history, especially the bAVMs-related primary symptom and operation history, will be recorded for the analysis of risk factors, as well as the past history, family history, smoking and drinking history. Morphological and location features of bAVMs will be interpreted by experienced radiologists and surgeons according to the images of cranial computed tomography (CT) and magnetic resonance (MR). Angioarchitecture features (origin and type of feeding arteries, situation of nidus and draining veins) will be specially evaluated by digital subtraction angiography. All image data will be stored in digital imaging and communications in medicine (Dicom) format. Milestones of management (dates of admission, operation, and discharge) will be recorded, and minute units will be used for the starting and finishing time of manipulations during the hybrid operation. Materials used in the endovascular and microsurgical procedures will be finely recorded in their type and quantity. Cases operated by a special manipulating technique will be labeled. The neural conditions and outcomes of participants will be evaluated by physicians using the modified Rankin Scale (mRS) and the National Institute of Health Stroke Scale (NIHSS) at the time of admission, 2 days after operation, 1 week after operation and at the follow-up time points after discharge. All data will be collected by full-time clinical research coordinators (CRCs) with both paper documents and a web-based electronic data capture system (EDC system), and they will be quality-controlled by clinical research associates (CRAs) from a third-party contract research organization (CRO). All participants will be informed, asked for written informed consent, and allowed to withdraw at any time.

### Inclusion criteria

patients aged≤70 years old;diagnosed with arteriovenous malformations (AVMs) in brain parenchyma (including cerebrum and cerebellum) by DSA, with/without dura arteriovenous fistula;with any operative indications as follows:with stable hematoma or history of hemorrhage due to bAVMs, and allowed selective operation;with recurrent epilepsy seizure, having failed treatment with antiepileptic drugs (AEDs);with induced deterioration of neurological functions;With Spetzler-Martin grades from I to IVWritten informed consent is provided by participant in person, or by legal guardians of whom is under 18 years old

### Exclusion criteria

> 70 years old with no significant hemorrhagic risk of bAVMs;with Spetzler-Martin Grade ≥ V;accompanied by severe chronic disease, organ dysfunction, or malignant tumor that cannot tolerate the operation;allergic to iodinated contrast agent;refuse to provide written informed consent by participant in person, or by legal guardians of whom is under 18 years old.

### Group assignment and treatment

In the registry set, patients will be assigned to the TO group or the HO group on the basis of clinical conditions and personal wishes. Patients in the HO group will receive microsurgical operation under the assistance of endovascular embolization or balloon occlusion. Patients in the TO group will receive only traditional microsurgical operations, and a repeated DSA will be arranged 3 days after the operation.

In the trial set, patients who refuse the randomized group assignment will be enrolled in the registry set. Those who agree will be randomly (by central randomization system) assigned to the TO group or the HO group. The interventions of each group will be the same in the two sets.

The functional MRI-based neuro-navigation and intraoperative Doppler ultrasound will be used as essential assistance in all operations.

### Outcome evaluation

The primary outcome is defined as neural function deterioration (an increased mRS and mRS > 2) in the 3 months after operation. The neural function will be evaluated 48 h and 7 days after operation while hospitalized and at 3 months, 6 months and 12 months after discharge. A deterioration will be considered temporary if it is sustained < 12 months, otherwise it will be considered permanent. The secondary outcomes will include the postoperative mortality, operation-related complications, and bAVMs residue. The postoperative mortality will include death that occurs within 7 days from the date of operation. Operation-related complications will include any complications that occur within 7 days from the date of operation, including intracranial hemorrhage or infarction, infection of the central nervous system, infection of the respiratory system, cranial nerve deficits, and other symptomatic complications. The bAVMs residue will be diagnosed on the basis of DSA or CTA after operation. The mRS fluctuation will also be recorded and defined as the consecutive changing value of mRS between different follow-up points. The evaluations and diagnoses will be conducted by the physicians who have not learnt about the patients and collected by CRCs.

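### Residue is defined without a common imaging modality or time point for the two groups, and, separately, a 7-day window leaves later deaths and complications out of both safety outcomes

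*Protocol article*

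**What the plan says.** Residue, mortality and operation-related complications are the secondary outcomes (Outcome evaluation).

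- **Residue:** "The bAVMs residue will be diagnosed on the basis of DSA or CTA after operation". No time point is given, and nothing says which modality applies to which patient.
- **Imaging by group** (Group assignment and treatment): for TO, "Patients in the TO group will receive only traditional microsurgical operations, and a repeated DSA will be arranged 3 days after the operation". For HO, the text describes treatment only: "Patients in the HO group will receive microsurgical operation under the assistance of endovascular embolization or balloon occlusion". The same section adds "The interventions of each group will be the same in the two sets", and Study design says that the registry and trial sets have common end points.
- **Mortality:** "The postoperative mortality will include death that occurs within 7 days from the date of operation".
- **Complications:** "Operation-related complications will include any complications that occur within 7 days from the date of operation".
- **Follow-up:** "The neural function will be evaluated 48 h and 7 days after operation while hospitalized and at 3 months, 6 months and 12 months after", where the later visits are counted from the patient leaving hospital. The primary outcome is a raised mRS that also exceeds 2, within 3 months of operation.

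**The concern.** There are two separate weaknesses.

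**Residue.** A between-group comparison of residue is fair only if residue is looked for in the same way and at the same time in both groups. As written, TO patients have a scheduled day-3 DSA, while HO patients may be judged on DSA or CTA at an unstated time. The plan itself relies on DSA for entry (Inclusion criteria) and for describing the angioarchitecture (Study participants). Residue is the only listed outcome that measures cure, and both the Abstract and the Discussion look forward to a higher cure rate. Because the arm-specific arrangements appear to carry over to the trial set, the randomized comparison could be affected as well as the registry.

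**Safety window.** Counting stops at day 7 in both groups. Some listed complications, such as central nervous system or respiratory infection, can appear later, and so can deaths. The plan keeps seeing these patients but does not count such events in either safety outcome.

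**Working it through.** The protocol gives no residue rate and no detection figures, so there is no stated number to reproduce. The passages are set side by side first. An illustration under declared assumptions follows.

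**1. Residue, side by side**

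| Item | TO | HO |
|---|---|---|
| Scheduled postoperative imaging | DSA, day 3 | none stated |
| Modality allowed for residue | DSA or CTA | DSA or CTA |
| Time point for residue | none in the definition | none in the definition |

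The two sections do not contradict each other, since a day-3 DSA satisfies the definition. The definition does, however, permit unequal ascertainment.

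**2. Size if ascertainment is unequal (illustration)**

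Let r be the true residue rate, equal in both groups. Take DSA detection as 100%, and let s be the detection of the other modality relative to DSA. Let f(HO) and f(TO) be the shares of each group judged on the other modality.

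Observed rate in a group = r × [1 − f × (1 − s)]

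Spurious difference, TO minus HO = r × (1 − s) × [f(HO) − f(TO)]

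In the extreme case f(HO) = 1 and f(TO) = 0:

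| r | s = 0.95 | s = 0.90 | s = 0.80 | s = 0.70 |
|---|---|---|---|---|
| 5% | 0.25 points | 0.5 | 1.0 | 1.5 |
| 10% | 0.5 | 1.0 | 2.0 | 3.0 |
| 20% | 1.0 | 2.0 | 4.0 | 6.0 |

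Example: r = 10% and s = 0.80 give 10% in TO and 0.10 × 0.80 = 8% in HO, with no true difference. If only half of HO is judged on the other modality, the gap halves to 1 point. If both groups use it equally, the gap is zero.

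**3. Chance of a false positive in favour of HO at 10% against 8%**

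This uses the normal approximation for two proportions at two-sided 0.05, so the nominal chance in this direction is 2.5%.

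- *Trial set, 236 / 2 = 118 per group.* Pooled rate 0.09. Null standard error √(0.09 × 0.91 × 2/118) = 0.0373. Alternative standard error √((0.09 + 0.0736)/118) = 0.0372. z = (0.02 − 1.96 × 0.0373)/0.0372 ≈ −1.42, which gives about 8%.
- *Registry set, 400 TO and 800 HO.* Pooled rate (40 + 64)/1200 = 0.0867. Null standard error √(0.0867 × 0.9133 × (1/400 + 1/800)) = 0.0172. Alternative standard error √(0.09/400 + 0.0736/800) = 0.0178. z = (0.02 − 1.96 × 0.0172)/0.0178 ≈ −0.77, which gives about 22%. Confounding in the non-randomized registry comes on top of this.

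**4. Safety window**

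No arithmetic applies.

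- A death on day 8 or later is not in the mortality outcome.
- A complication on day 8 or later is not in the complication outcome.
- The primary outcome fills only part of the gap. A later complication that leaves the mRS at 2 or below does not meet it. A death within 3 months would meet it only if death is scored on the mRS, which the article does not state.

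**The case against.** **HO imaging is inferred from silence.** The article is condensed, and the full protocol may hold the HO schedule. HO combines microsurgery and endovascular work in one session (Background), so angiography during the operation is possible. The word repeated, applied to the TO angiogram, may hint at a counterpart in HO. This stands. A reader might infer that residue is searched for harder in TO and that the comparison is biased toward HO. The article does not say that HO residue is judged on CTA, so that inference is not supported. Even with intraoperative DSA in HO, though, the time of assessment would differ from day 3 in TO, and the outcome definition would still fix neither modality nor time.

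**Assessors are blinded.** This is true, and useful against reading bias. It does not help here, because a blinded reader cannot see what the modality did not show.

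**The 7-day limit is the same in both groups.** This also stands. A reader might infer that all the secondary outcomes are measured differently by group; only residue can be. A reader might also suppose that the limit works against one group through re-treatment of residue found on day 3. The article describes no re-treatment pathway, and any re-treatment on days 3 to 7 would fall inside the window.

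**Later neurological harm is followed.** The mRS is recorded to 12 months after discharge, so disabling harm is not lost. What escapes is later death as a named outcome, and later complications that do not disable.

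**Conclusion.** Both weaknesses hold, as separate points.

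1. **Residue.** The definition allows the groups to be compared on different modality and timing, and blinding does not remove this. Bias toward HO follows only if HO is judged more often on a less sensitive modality. In the extreme case, over assumed residue of 5% to 20% and relative detection of 70% to 95%, the spurious difference is 0.25 to 6 points. None of these rates comes from the protocol. The result illustrates a risk and is not an estimate of bias.
2. **Safety window.** The 7-day limit under-counts deaths and complications equally by definition in both groups. It is too short for the follow-up planned, but it is not differential measurement.

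The primary outcome, its sample size and its test are not affected. The changes should be made because residue carries the cure claim and the two safety outcomes carry much of the risk assessment.

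**What to change.** **Residue.** Reconcile the sections on group assignment and outcome evaluation.

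- Define the between-group outcome by one modality and one time window that apply to both groups, using images already obtained and read without group labels where possible.
- Before fixing the rule, check which images both groups actually have. A rule that few HO patients can meet would leave most of them unverified, and a rule that pairs intraoperative HO images with day-3 TO images would leave the timing unequal.
- Report modality and timing by group.
- Present results that rest on another modality separately or in a sensitivity analysis.
- If no common modality and window exist, say so and report residue descriptively by group.

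**Safety.** Also count deaths and operation-related complications to 30 days after operation and to the existing 3-month visit in both groups. The 30-day count can be built from event dates collected at that visit. Keep the 7-day figures, and state how death is scored in the mRS outcome.

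**Cost.** Revised definitions and extra date fields on the case report form. Event rates will look higher, and some residue results will be classed as unverified. No new visit or procedure is required.
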